## Abstract

**Background:**

Many patients struggle to understand referral letters and discharge summaries; low health literacy is prevalent, and short consultations limit explanations. Large language models (LLMs) can translate clinical jargon into layperson language, but their impact on doctor–patient communication in real care remains untested.

**Objective:**

This study aims to determine whether providing an artificial intelligence (AI)–generated, medically validated layperson-language translation of key medical documents before a consultation improves the quality of doctor–patient communication.

**Methods:**

We plan to conduct two single-center, parallel-group randomized controlled trials in neurosurgery: AI-INFOCARE (outpatients prior to treatment discussions) and AI-MEDTALK (inpatients at surgical discharge). Adults (aged 18 years or older, German-speaking, and able to consent) are randomized 1:1 to receive either (1) an AI-generated layperson-friendly summary of their referral or discharge document in addition to usual care or (2) usual care only. Summaries are produced with a Claude-based system (Simply Onno GmbH) and undergo human verification against the source document using a predefined checklist. The primary outcome is patient-rated interaction quality (Fragebogen zur Arzt-Patient-Interaktion/Questionnaire on the Quality of Physician–Patient Interaction) immediately postconsultation. Secondary outcomes are perceived autonomy support (brief Health Care Climate Questionnaire), self-rated understanding (5-point item), physician-rated encounter difficulty (Difficult Doctor–Patient Relationship Questionnaire, 10-item), and consultation length (minutes). Randomization uses a computer-generated allocation list with concealed, sequential assignment at the point of inclusion; recruiting clinicians have no access to the sequence, and analysts are blinded to group codes. Fidelity is assured by standard operating procedures, rater training, and periodic dual review with interrater agreement estimates. Safety monitoring defines information-related adverse events (eg, distress requiring unplanned clinical support or clinically relevant inaccuracies) and includes an independent safety overseer. Ethics approvals were obtained in February 2025 from the ethics committee of Technische Universität Dresden, and both trials are registered in the German Clinical Trials Register.

**Results:**

Each trial targets 300 participants (150 per arm), providing greater than 80% power for an effect size *d*≈0.4 on the primary outcome (α=0.05). Outcomes are assessed immediately after the index consultation, with no additional follow-up planned in this protocol. We hypothesize that providing layperson-friendly summaries will significantly improve patients’ understanding and satisfaction with information, foster a more autonomy-supportive communication climate, and reduce physicians’ perceived difficulty in the encounter without unduly prolonging consultation time. Neither study received external funding. Both trials are currently in the recruitment phase, with patient enrollment scheduled to begin in May 2025 and expected to conclude by February 2026. Results are anticipated to be published in summer 2026.

**Conclusions:**

These pragmatic randomized controlled trials test a scalable AI intervention to strengthen understanding and interaction quality without adding clinician burden. If effective, AI-assisted layperson summaries could be integrated into routine workflows to advance health literacy and patient-centered care.

**Trial Registration:**

Deutsches Register Klinischer Studien DRKS00036810; https://www.drks.de/search/de/trial/DRKS00036810 and Deutsches Register Klinischer Studien DRKS00036814; https://drks.de/search/de/trial/DRKS00036814

**International Registered Report Identifier (IRRID):**

PRR1-10.2196/77204

## Introduction

Quality communication between physicians and patients is a cornerstone of effective health care. It is well documented that better doctor–patient communication improves patient understanding, satisfaction, adherence to treatment, and even clinical outcomes [1]. Conversely, communication breakdowns can undermine the therapeutic relationship and health results. Effective communication serves multiple purposes: building a good interpersonal relationship, exchanging information, and engaging patients in decision-making [2]. Achieving these goals requires that patients comprehend the information conveyed.

However, many patients struggle to understand complex medical terminology used in both verbal consultations and written documents such as specialist referral letters, procedure reports, or hospital discharge summaries. In Germany and internationally, limited health literacy is a pervasive challenge. A recent national survey found that 58.8% of German adults have inadequate health literacy, reporting difficulty understanding and using health information [3]. Such low health literacy is associated with poorer communication, lower patient engagement, and worse health outcomes [3]. Schaeffer et al [3] noted that improving the understandability of patient information is urgently needed to address this gap.

Doctor–patient communication can be conceptualized through the dual lenses of health literacy and shared decision-making (SDM). According to Leventhal’s Common-Sense Model and SDM frameworks, understandable information is a prerequisite for autonomy support and meaningful participation in care. Our outcomes map onto these constructs: the Fragebogen zur Arzt-Patient-Interaktion (FAPI)/Questionnaire on the Quality of Physician–Patient Interaction (QQPPI) captures interaction quality, the brief Health Care Climate Questionnaire (HCCQ) reflects autonomy support, and self-rated understanding measures the informational pathway. By improving document comprehensibility before an encounter, the intervention directly targets these theoretical pathways expected to enhance both informational and relational aspects of communication.

Compounding the issue, physicians often face severe time constraints during appointments. Germany is among the countries with the shortest primary care visit lengths, historically averaging only about 7 to 10 minutes per patient [4]. This limited time makes it difficult to explain diagnoses and treatments in depth, especially if patients are encountering complex information for the first time. Studies indicate that physicians feel pressure to cover medical content quickly, which can lead to inadequate explanations and patients leaving with unanswered questions [4]. Time pressure has been linked to decreased patient recall and satisfaction [1]. Many patients turn to external sources, such as the internet, for clarification, which may yield unreliable information (“[name]”). In the worst cases, misunderstanding or lack of information can cause patient anxiety, unnecessary repeat consultations, or even nonadherence and premature therapy discontinuation [5,6].

Written medical documents are a key part of doctor–patient communication but are often written primarily for other health care professionals, not laypersons. For example, a hospital discharge letter typically contains medical jargon, abbreviations, and complex narrative that an average patient finds hard to decipher. This information gap represents a missed opportunity: if patients could better understand their medical records, they would be more empowered during follow-up visits with their doctors. Past efforts to improve this have included manually creating simplified, patient-friendly discharge letters. A preliminary trial in Austria demonstrated that providing patients (or proxies) with a simplified discharge summary significantly improved their acceptance of and satisfaction with the information compared to the standard technical letter [7]. Participants valued the clearer structure, avoidance of abbreviations, and layperson language, indicating that patient-friendly documents enhance communication.

Recent advances in artificial intelligence (AI) now enable automated translation of complex text into simpler language. Large language models (LLMs) such as GPT-4, Gemini, Llama, and Claude can parse medical text and generate explanations in more digestible terms. Early studies suggest that AI-generated summaries can dramatically improve readability. Zaretsky et al [8] showed that an LLM-transformed discharge summary achieved a mean reading level of sixth grade versus eleventh grade for the original and an understandability score of 81% versus 13%, without losing accuracy (although some errors occurred). Similarly, a Korean study found that ChatGPT could produce patient-friendly discharge notes that were easier to read, highlighting AI’s potential in multilingual settings. These findings underscore that AI can serve as a powerful tool to bridge the language gap in medical communication, provided its outputs are properly validated for accuracy and completeness [8]. Compared with manual simplification approaches, which improve comprehension but are resource-intensive and difficult to scale, LLM-based systems offer immediate generation at low marginal cost. However, AI introduces distinct risks, such as hallucinations or omissions, which necessitate systematic human validation. Our protocol therefore emphasizes a fidelity process with predefined checklists, dual review of samples, and correction logging to balance scalability with safety.

To our knowledge, no completed randomized controlled trials (RCTs) have yet evaluated AI-generated, medically validated layperson translations of medical documents delivered before real-world consultations. However, related trials in digital health literacy and patient-oriented discharge summaries are ongoing or recently registered, underscoring the timeliness and originality of this study. For example, in Germany, study DRKS00035739 (“PALLADS”) is currently recruiting and testing whether LLM-assisted simplification of discharge summaries improves patient activation; similarly, NCT06859216 examines AI-generated plain-language versions of ophthalmology notes. These confirm that although related trials are underway, none to date have completed RCTs of AI-generated, medically validated layperson translations of referral or discharge documents delivered before real-world consultations. The AI-INFOCARE and AI-MEDTALK trials have been conceived to fill this gap. These two parallel RCTs will test the central hypothesis that giving patients an easy-to-understand version of their medical documents before they speak with their doctor will lead to more effective and satisfying communication during the consultation. Specifically, we expect that patients with the AI-assisted information will feel more informed and autonomous, ask better questions, and overall experience a better-quality interaction with their physician, whereas doctors may perceive less difficulty in explaining and managing the visit.

Both trials are prospective, two-arm randomized controlled studies conducted at a large academic medical center in Germany (the Neurosurgery Clinic at Universitätsklinikum Carl Gustav Carus, Dresden). Importantly, they address two complementary patient populations and clinical contexts: AI-INFOCARE focuses on outpatients about to undergo treatment (improving understanding before a treatment discussion), whereas AI-MEDTALK focuses on inpatients at discharge after surgery (improving understanding of what happened and next steps). By covering both “front-end” and “back-end” clinical scenarios, the trials together aim to generate broadly applicable evidence on this AI intervention.

If successful, these studies will produce evidence for a scalable digital health intervention that could be implemented across various settings to improve patient comprehension and engagement. Enhancing communication in this way aligns with public health goals of improving health literacy and patient-centered care. Ultimately, clearer initial understanding can reduce follow-up questions, prevent misinformed decisions, and strengthen the therapeutic alliance [1]. We also acknowledge potential challenges: for instance, doctors must trust and verify AI outputs (to avoid any misinformation), and workflows must integrate generating and sharing summaries without causing delays. The Discussion section will address these considerations.

In summary, the trials will test an innovative strategy to achieve the age-old goal of “understanding instead of uncertainty” in health care communication. This manuscript presents the detailed protocol following SPIRIT guidelines, including rationale, methods, and planned analyses for AI-INFOCARE and AI-MEDTALK.

## Methods

### Ethical Considerations

This study was approved by the ethics committee of Technische Universität Dresden. The approval numbers are AI-INFOCARE: BOff(Mono)-EK-89022025 and AI-MEDTALK, BOff(Mono) -EK-91022025. The study protocol was prepared in accordance with SPIRIT (Standard Protocol Items: Recommendations for Interventional Trials) guidelines for clinical trial protocols and approved by the Technische Universität Dresden ethics committee in February 2025. Both trials are registered in the German Clinical Trials Register (DRKS00036810 and DRKS00036814). All participants will provide informed consent. We take care to ensure the intervention does not negatively impact care: the AI summaries are provided in addition to usual explanations, not replacing physician communication. Physicians are instructed to verify and correct any misunderstanding. We also ensure confidentiality of patient data; the AI processing is conducted on a General Data Protection Regulation/Datenschutz-Grundverordnung–compliant server, and no data are shared beyond the study team. Potential risks to participants are minimal—there is a slight risk that a patient might misinterpret an AI summary if it contained a minor error, but our human verification mitigates this. We also considered the psychological impact: for instance, reading one’s medical details in plain language could be distressing if the news is bad (eg, diagnosis of a serious illness). In standard care, patients might not fully grasp the seriousness from the medical jargon, whereas the plain summary could make it clear. This is ethically complex, but we believe transparency is ultimately better for informed decision-making. Doctors will be available to discuss any concerns raised by reading the summary. Indeed, this may prompt important discussions that otherwise would not have occurred.

We define information-related adverse events (AEs) as (1) patient distress from the summary requiring unplanned clinical support during or after the visit, (2) clinically relevant inaccuracies identified in the summary, or (3) formal complaints linked to the intervention. All AEs are recorded on standardized forms and reviewed quarterly by an independent safety overseer; serious AEs are reported within 72 hours.

No monetary compensation is provided, but we find that patients are generally eager to participate in order to possibly receive a clearer explanation.

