### Study Design and Setting

Both AI-INFOCARE and AI-MEDTALK are designed as prospective, parallel-group RCTs. The trials share a common overall design, with nearly identical interventions and outcomes, but target different patient populations and phases of care (outpatient pretreatment vs inpatient discharge). The study setting is the Department of Neurosurgery at University Hospital Carl Gustav Carus, Technische Universität Dresden, Germany, which includes outpatient clinics and inpatient wards. The trials are investigator-initiated collaborations between the hospital and Simply Onno GmbH (Berlin; [9]), a health AI startup.

The overall structure of the trials is summarized in Figure 1. Each trial will enroll participants over a 6-month recruitment period and follow a simple two-arm randomized design (intervention vs control). There is no blinding (open-label) and no crossover between arms. Outcome assessments are conducted at a single postintervention time point (immediately after the index doctor–patient consultation during which the intervention could have an effect). There are no long-term follow-ups in this protocol, as the primary focus is on the immediate communication outcomes of the consultation.

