#### Control (Usual Care)

Participants randomized to the control arm go through usual care procedures without any additional intervention. For outpatients, this means they have whatever documents they normally would (often patients do bring their referral letter or test results, but these are in technical language, and we do not provide any translated version). They will have their consultation with the doctor using those standard materials. For inpatients, usual care means they receive the standard discharge summary at the end of the discharge discussion (or sometimes given to them to hand to their next doctor), but not ahead of time in simplified form. Essentially, the control group represents the status quo: the patient relies on the doctor’s oral explanation during the consultation and on the standard medical documents, with no separate plain-language text.

All other aspects of care are identical between groups. Both groups’ consultations take place with the same pool of physicians (neurosurgery attendings or senior residents), in the same settings. Physicians will have the original medical documents in both cases for reference. After the consultation, both groups complete the outcome questionnaires described below.

Notably, if a patient in the control group expresses strong confusion about their medical documents or requests an explanation in writing, the physician will handle it per usual care (which might involve some oral explanation or writing brief notes, but the prepared AI summary will not be provided at that point, to preserve the integrity of the comparison). However, at the end of the study, control patients will be offered the layperson-friendly summary if they desire, as an ethical consideration to avoid denying potentially helpful information.

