#### Effects on Consultation Dynamics

We assume the effect is positive, but it is possible some doctors or patients might react unexpectedly. A doctor might feel that the patient’s preknowledge encroaches on their explanatory routine, or a patient might feel overloaded if they read a lot before the talk. It is a delicate balance—one could liken it to giving patients laboratory results directly before talking to the doctor; some studies show patients prefer knowing results beforehand, while others caution that it can raise anxiety. Our trials will provide insight on this. Through the FAPI and qualitative feedback, we will see if any negative sentiments arise, for example, a patient could say “reading it alone made me worried.” We believe the net effect is beneficial as long as the subsequent conversation addresses any anxiety the information caused. Indeed, knowing what to be worried about can lead to addressing it head-on with the physician, which is ultimately good.

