#### Risk of Workflow Disruption

Another important limitation is the risk of workflow disruption. Physicians may experience additional cognitive load from reviewing AI outputs, and patients may experience heightened anxiety if sensitive diagnoses are clearly stated. Furthermore, AI errors, even if rare, could undermine trust. These risks are integral to the evaluation and will be systematically monitored through the fidelity audit and AE reporting.

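### The distress adverse event counts only distress attributed to the summary, so there is no control rate for the psychological harm the protocol names

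*Protocol article*

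**What the plan says.** Ethical Considerations lists three kinds of information-related adverse event:

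1. "patient distress from the summary requiring unplanned clinical support during or after the visit"
2. "clinically relevant inaccuracies identified in the summary"
3. "formal complaints linked to the intervention"

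All are entered on standardized forms and reviewed quarterly by an independent safety overseer, with serious events reported within 72 hours. The same section gives the reason for concern as a contrast with usual care: jargon may hide how serious a finding is, and a plain summary may reveal it.

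Under Control (Usual Care): "Participants randomized to the control arm go through usual care procedures without any additional intervention". Controls are offered the summary only at the end of the study.

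Risk of Workflow Disruption names heightened patient anxiety among the risks that "will be systematically monitored through the fidelity audit and AE reporting".

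Two other places word the event differently. The abstract has no attribution to the summary in its distress example: "Safety monitoring defines information-related adverse events (eg, distress requiring unplanned clinical support or clinically relevant inaccuracies". The Results section names a patient being very upset on understanding the diagnosis as a potential adverse outcome, and in the same sentence treats such reactions as part of informed care.

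**The concern.** Neurosurgical consultations can carry bad news in either arm, so some patients may need unplanned support whether or not they read a summary. The protocol's own worry is comparative: does plain language add distress to what usual care already produces? Answering that needs the same event counted in the same way in both arms. Item (1) builds the cause into the definition, so the event can arise in one arm only. A count from the intervention arm then cannot be separated into background and effect, and its size depends on how readily someone ascribes distress to the summary. The protocol itself fixes this definition, so it is not a detail left to an analysis plan.

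**Working it through.** **Inputs.** From the document: 150 patients per arm in each trial, 1:1 allocation, and the definitions above. The document states no adverse event or distress rate, so there is no figure of the plan's to reproduce. All rates below are assumptions, with a range.

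**Step 1. Can a control meet each item?**

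| Item | Tied to | Control patient during the assessed visit |
|---|---|---|
| (1) distress | the summary | cannot be counted |
| (2) inaccuracy | the summary text | not applicable, and rightly so |
| (3) complaint | the intervention | conceivable, e.g. a complaint about not receiving a summary |

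Only for item (1) is the zero strict in a way that matters. It holds until a control takes up the late offer of the summary.

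**Step 2. Does another measure fill the gap?** FAPI measures interaction quality and the brief HCCQ autonomy support. The remaining outcomes are one self-rated understanding item, physician-rated difficulty (DDPRQ-10) and consultation time. None measures distress. The debrief described under Secondary Outcome 4 is put to the intervention group only. The fidelity checklist covers accuracy and completeness of the text. Of the two channels named under Risk of Workflow Disruption, only adverse event reporting could register a patient's distress.

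**Step 3. What would the count show if the summary had no effect?** Let p be the true rate of distress needing support, equal in both arms, and s the share of intervention-arm cases attributed to the summary. The expected intervention count is 150 × p × s; the control count is 0 by definition. Fisher's exact test (two-sided) gives p = 0.060 for 5/150 against 0/150 and p = 0.030 for 6/150 against 0/150, so six is the smallest count that would look significant.

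| p (assumed) | s (assumed) | Expected count | P(6 or more), Binomial(150, p × s) |
|---|---|---|---|
| 2% | 0.5 | 1.5 | 0.004 |
| 2% | 1.0 | 3.0 | 0.08 |
| 5% | 0.5 | 3.75 | 0.17 |
| 5% | 1.0 | 7.5 | 0.77 |
| 10% | 0.5 | 7.5 | 0.77 |
| 10% | 1.0 | 15 | 0.998 |

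With no true difference, the result runs from almost never to almost always significant, depending on p and s. In the other direction, if such reactions are classed as part of informed care, s falls and a real excess would go unrecorded.

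**Step 4. What can a one-arm count support?** Clopper-Pearson 95% limits for 8/150 (an illustrative count) are 2.3% to 10.2%. For 0/150 the upper limit is 1 − 0.025^(1/150) = 2.4%. These describe attributed events in one arm and have nothing to be set against.

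**Step 5. What would recording in both arms deliver?** Power is Φ[(d − 1.96·se0)/se1], where d is the difference in rates and se0 and se1 are the pooled and unpooled standard errors. For 5% against 14.6%, 150 per arm:

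- d = 0.096 and pooled rate 0.098
- se0 = √(0.098 × 0.902 × 2/150) = 0.0343
- se1 = √[(0.05 × 0.95 + 0.146 × 0.854)/150] = 0.0339
- (0.096 − 1.96 × 0.0343)/0.0339 ≈ 0.85, so power ≈ 0.80

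| Control rate (assumed) | Rate detectable with 80% power, 150 per arm | 300 per arm (both trials pooled) |
|---|---|---|
| 1% | 7.6% | 4.9% |
| 2% | 9.6% | 6.7% |
| 5% | 14.6% | 11.3% |
| 10% | 21.8% | 18.0% |

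If both arms were at 5%, the 95% interval for the difference would extend 1.96 × √(2 × 0.05 × 0.95/150) = 4.9 percentage points either side.

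**The case against.** The best defence is that the protocol sets up surveillance, not a safety comparison. Its objective, hypotheses and outcomes concern communication. Attributed events on a form, reviewed by an independent overseer, serve to catch individual harm, and the text on anxiety promises monitoring rather than a test between arms. That stands as far as it goes. It does not remove the gap, because the protocol states the risk relative to standard care and calls it integral to the evaluation.

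Several stronger readings are tempting but not supported:

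- **That no control can have any information-related event.** Strict only for item (1). Item (2) belongs to the intervention arm, and a control could meet item (3).
- **That Effects on Consultation Dynamics promises an answer through adverse events.** It says "Our trials will provide insight on this", but the route it names is FAPI and qualitative feedback. FAPI is collected in both arms, so that route has a comparator, though FAPI is not a distress scale.
- **That counting events after the visit contradicts the design.** "There are no long-term follow-ups in this protocol" sits in a paragraph on outcome assessment and excludes long-term follow-up only. Nothing says event capture ends when the patient leaves, and Expected Outcomes and Future Directions foresees some data on contacts after discharge.
- **That unblinded staff make the attribution.** The trials are open-label, but the document does not say who attributes.

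It is also fair to say that the repaired comparison would be too coarse to detect any but a large excess.

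**Conclusion.** The point holds for the distress event. As defined, it yields no control rate for the psychological harm the protocol itself names, and no other measure supplies one. The abstract, Ethical Considerations and Results wordings also need to be reconciled. Step 3 shows that comparing the present counts between arms would reflect the attribution rule rather than the summary's effect. The sizes rest on assumed background rates of 2% to 10% and assumed attribution shares; the structural gap rests on no assumption. The overseer's review of individual events is unaffected, as is the primary analysis. This is a worthwhile, inexpensive improvement, not a flaw in the main comparison.

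**What to change.** - Define item (1) as distress requiring unplanned clinical support, whatever its presumed cause, and item (3) as a formal complaint about the information given.
- Record both in both arms, by the same procedure, on the existing standardized form. State one window that is the same for each arm, and do not make it narrower than the present capture during or after the visit. Ending it when the patient leaves would lose later complaints and later distress that the current wording admits.
- Record relatedness to the summary as a separate field, so that the overseer keeps the present signal.
- Keep item (2) as an intervention-arm measure.
- Report counts per arm with exact confidence intervals, descriptively and without a powered test.
- Align the abstract, Ethical Considerations, Results and Risk of Workflow Disruption, including whether being very upset by a diagnosis is recorded as an event.

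The cost is some extra forms for control patients and staff time to complete them. No instrument, visit or sample size changes. The remaining limitation is precision, as shown in Step 5.
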